### **3.3 EFFICACY ANALYSIS**

Primary efficacy analysis at one year is referred to TKV absolute change from time 0 (Visit 2) to 12 months (Visit 7). Primary efficacy analysis at three years is referred to the measured GFR slope from time 0 (Visit 2) onward.

#### **3.3.1.1 One Year Primary Efficacy Parameter**

The short-term primary efficacy variable at one year, i.e. absolute change at 12 months from baseline in TKV, will be compared between the treatment groups using analysis of covariance (ANCOVA) model of the log-transformed TKV, including baseline TKV, age and gender as covariates. Details including least square means and standard errors, and covariate coefficients, standard errors, p-values and 95% confidence intervals will be provided respectively. (Senn (1997)). In case of departure from Normality assumptions in the log-transformed TKV distribution a non parametric approach will be used instead. Summary statistics, namely mean (sd), median, q1, q3, minimum, and

maximum for TKV and absolute TKV change from baseline to six months will be tabulated by nominal visit and treatment group (Tables 3.1.1-3.1.3).

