### **3.2 ANALYSIS SPECIFICATIONS**

Assumptions underlying all parametric analyses will be checked and transformations to normality (e.g. log-transformation) or non-parametric methods used, where violations of assumptions are seen.

For efficacy analyses based on the Full Analysis Set, no imputation of missing values will be performed. The last available data value will be used to calculate the time to onset of an event.

For both the analyses based on the Full Analysis Set and the Per Protocol Set, visit windows will not be used and data points will be classified according to the named (nominal) visit.

All statistical tests will be two-sided unless otherwise stated.

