#### **3.3.2.7 TKV and absolute and percent changes in TKV (Tables 3.39.1 to 3.39.3)**

Summary statistics, namely mean (sd), median, q1, q3, minimum, and maximum for TKV and TKV absolute and percent changes from baseline onward will be tabulated by nominal visit and treatment group.

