|       | Absolute change (mL)    | --                 | xx.xx (xx.xx)
xx.xx [x.x to x.x] | xx.xx (xx.xx)
xx.xx [x.x to x.x] | --                 | xx.xx (xx.xx)
xx.xx [x.x to x.x] |
|       | Annual slope (mL/year)  |                    |                                     | xx.xx (xx.xx)
xx.xx [x.x to x.x] |                    |                                     |
|       | Chronic slope (mL/year) |                    |                                     | xx.xx (xx.xx)
xx.xx [x.x to x.x] |                    |                                     |
| htTKV | Mean (SD) (mL)          | xx.xx (xx.xx)      | xx.xx (xx.xx)                       | xx.xx (xx.xx)                       | xx.xx (xx.xx)      | xx.xx (xx.xx)                       |
|       | Median [IQR]            | xx.xx [x.x to x.x] | xx.xx [x.x to x.x]                  | xx.xx [x.x to x.x]                  | xx.xx [x.x to x.x] | xx.xx [x.x to x.x]                  |
|       | p value vs.plac. at 1 y |                    |                                     |                                     |                    |                                     |
|       | p value vs.plac. at 3 y |                    |                                     |                                     |                    |                                     |
|       |                         |                    |                                     |                                     |                    |                                     |
|       | Absolute change (mL)    | --                 | xx.xx (xx.xx)
xx.xx [x.x to x.x] | xx.xx (xx.xx)
xx.xx [x.x to x.x] | --                 | xx.xx (xx.xx)
xx.xx [x.x to x.x] |
|       | Annual slope (mL/year)  |                    |                                     | xx.xx (xx.xx)
xx.xx [x.x to x.x] |                    |                                     |
|       | Chronic slope (mL/year) |                    |                                     | xx.xx (xx.xx)
xx.xx [x.x to x.x] |                    |                                     |

TKV, Total Kidney Volume; htTKV, Height –adjusted Total Kidney Volume

**Table 3.1.2** TKV and height-adjusted TKV, and absolute changes in kidney and cyst volume in participants randomized to Octreotide-LAR or placebo. Stratum: CCC absent

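### The 1-year primary endpoint is absolute TKV change in mL, but the stated model is on the log scale, with the baseline scale unstated and an open non-parametric fallback

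*Supplement*

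**What the plan says.** SAP section 3.3 sets the 1-year primary efficacy analysis on "TKV absolute change from time 0 (Visit 2) to 12 months". Section 3.3.1.1 repeats the variable as "absolute change at 12 months from baseline in TKV" and says that it will be compared between arms "using analysis of covariance (ANCOVA) model of the log-transformed TKV, including baseline TKV, age and gender as covariates". Least-squares means, coefficients and 95% confidence intervals are promised from that model.

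The same section gives the fallback: "In case of departure from Normality assumptions in the log-transformed TKV distribution a non parametric approach will be used instead". Section 3.2 adds a general rule for parametric analyses, with "transformations to normality (e.g. log-transformation) or non-parametric methods used, where violations of assumptions are seen".

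Absolute change appears elsewhere only as description. Section 3.3.2.7 says that "TKV and TKV absolute and percent changes from baseline onward will be tabulated by nominal visit and treatment group". The templates for Tables 3.1.1 to 3.1.3 have an absolute-change row in mL for each arm, but their p-value rows against placebo sit beneath the TKV level, above the change row.

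**The concern.** Three parts of the primary analysis do not fit together.

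- **Endpoint and model.** A model for log TKV gives an adjusted difference in mean log TKV, which back-transforms to a ratio. It does not give a difference in mL change, and no conversion to mL is described.
- **Baseline covariate.** Only the response is said to be logged. After one year log TKV should be close to linear in log baseline and curved in raw baseline, so a raw covariate would leave baseline variation in the residual.
- **Fallback.** ANCOVA needs well-behaved residuals, not a Normal marginal distribution of the response. The trigger names the latter, and the method it leads to is not named.

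At stake are what the primary result means, possibly its power, and how far the primary test is fixed before the data are seen. Two competent analysts could deliver different primary tests from this text.

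**Working it through.** The documents state no sample size, SD, effect size or power for TKV, so there is no figure to reproduce. Inputs:

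| Input | Value | Source |
|---|---|---|
| Endpoint | 12-month change in TKV, mL | SAP 3.3, 3.3.1.1; Table 3.1.1 template |
| Response | log TKV | SAP 3.3.1.1 |
| Baseline scale | not stated | SAP 3.3.1.1 |
| Allocation, sidedness | 1:1, two-sided | SAP sections 1 and 3.2 |
| SD of log baseline TKV, *s* | 0.2 to 0.8 | assumed |
| SD of 1-year log growth, *e* | 0.04 to 0.15 | assumed |
| Patients per arm | 40 or 50 | assumed |
| Log effect, control growth, median TKV | -0.04, 0.06, 2000 mL | assumed |
| Test level | 0.05 | assumed for TKV; stated only under the time-to-event tables |

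**1. Scale of the estimate.** In simulated trials with the same log effect of -0.04 (40 per arm, *e* = 0.06), the mean mL difference was about -85 mL at *s* = 0.2 and -99 mL at *s* = 0.6. One ratio therefore corresponds to different mL differences, depending on the baseline distribution. The log model alone does not report the declared quantity.

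**2. Cost of a raw baseline.** Take baseline X as log-normal and log TKV at 12 months as log X plus growth, treatment effect and noise of SD *e*. Then:

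- R² of log X on X = s²/(exp(s²) - 1)
- residual variance with log baseline = e²
- residual variance with raw baseline = e² + s²(1 - R²)
- relative efficiency (RE), raw against log = e²/[e² + s²(1 - R²)]

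Example, *s* = 0.5 and *e* = 0.06: R² = 0.25/(exp(0.25) - 1) = 0.25/0.2840 = 0.880. Lack-of-fit SD = 0.5 × √0.120 = 0.173. RE = 0.0036/(0.0036 + 0.0299) = 0.11.

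| *s* | RE, *e* = 0.06 | SE inflation, *e* = 0.06 | RE, *e* = 0.10 | RE, *e* = 0.15 |
|---|---|---|---|---|
| 0.2 | 0.82 | 1.10 | 0.93 | 0.97 |
| 0.3 | 0.47 | 1.45 | 0.71 | 0.85 |
| 0.4 | 0.22 | 2.11 | 0.45 | 0.64 |
| 0.5 | 0.11 | 3.05 | 0.25 | 0.43 |

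More than half the information is lost when *s* is at least 0.4 with *e* up to 0.10, or at least 0.5 with *e* up to 0.15. It is not lost at *s* = 0.2 for any *e* in the range, nor at *s* = 0.3 with *e* of 0.08 or more.

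**3. Simulation.** Power at 40 per arm, *e* = 0.06, log effect -0.04, 3,000 replicates, age and gender omitted:

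| *s* | log TKV on raw baseline | log TKV on log baseline | mL change on baseline TKV |
|---|---|---|---|
| 0.2 | 75% | 82% | 81% |
| 0.3 | 57% | 84% | 81% |
| 0.5 | 18% | 84% | 74% |
| 0.6 | 12% | 85% | 71% |

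Under no effect (1,500 replicates per setting) the rejection rate lay between 0.039 and 0.062 across all models and settings. The Monte Carlo standard error is √(0.05 × 0.95/1500) = 0.0056, so this is compatible with 5%. The log effect was essentially unbiased.

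**The case against.** The strongest reply is that an untransformed baseline is an inference. Having just called TKV log-transformed, the sentence can be read as using TKV on that scale throughout. This stands as far as it goes: if log baseline was meant, the precision loss disappears. The mismatch with the mL endpoint does not.

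A reader might also infer that the analysis is bound to lose most of its precision. The documents do not support that. They give no TKV variance or sample size, and the loss is small when baseline spread is narrow.

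Absolute change is not absent from the plan: it is tabulated by arm, and confidence intervals are promised. But those intervals come from the log model, and the mL figures are per-arm summaries. The unnamed fallback might be applied to the mL change, so one cannot say that the declared endpoint would go unestimated on every branch.

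Nor can one say that the fallback carries no baseline adjustment. A rank ANCOVA is also non-parametric, so the fair statement is that none is specified. Section 3.2 promises to check the assumptions of parametric analyses, which could include residuals. Section 3.3.1.1, however, is more specific and names the log-TKV distribution, and both sections leave the replacement method open.

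Finally, the SAP introduction schedules a review at the blind-review stage. That is an occasion to settle the wording, but does not itself settle it.

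**Conclusion.** The point holds in a limited form. From the text alone: the declared endpoint is a change in mL, the specified model estimates a ratio of geometric means, and nothing else in the plan supplies a between-arm mL difference with an interval. Also from the text alone: the scale of the baseline covariate is unstated, the fallback trigger looks at the wrong distribution, and the fallback method is unnamed.

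The precision cost is conditional on baseline TKV being entered raw, on log-normal baseline with proportional growth, and on the assumed SDs. At a log-growth SD of 0.06, relative efficiency runs from 0.82 to 0.11 as log-baseline SD goes from 0.2 to 0.5. A reader might go further and call the primary test invalid. The calculation does not support this, since type I error holds. The issue is what is estimated, possibly with what power, and how firmly the method is fixed in advance.

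**What to change.** Before unblinding, choose one of two consistent specifications.

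- **(a) Keep the mL endpoint.** Fit ANCOVA of 12-month mL change on treatment, baseline TKV, age, gender and randomisation stratum. Report the adjusted between-arm difference in mL with its 95% confidence interval. Give log TKV at 12 months on log baseline TKV as the supportive analysis.
- **(b) Keep the log model.** Use log(baseline TKV) with the same other covariates, and restate the primary effect as a ratio or percent difference. Give the adjusted mL difference with its interval alongside.

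Under either option, judge assumptions on model residuals and replace the open switch with a named sensitivity analysis: a rank ANCOVA adjusted for baseline. The stratum belongs in the model because patients are randomised within it.

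The cost is a few sentences of SAP text and a table row for the between-arm difference, with no new data. Option (a) leaves the declared endpoint as it is and gives up some power if growth is proportional (74% against 84% at *s* = 0.5 in the simulation above). Option (b) recovers that power but changes the declared estimand. That is the sponsor's choice and should be recorded as such.

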**INTRODUCTION**

---

This study is a multi-centre, prospective, randomised double-blind parallel-group comparison of long acting somatostatin analogue (Octreotide LAR) and placebo.

The study is coordinated by the Clinical Research Center for Rare Diseases of the Mario Negri Institute for Pharmacological Research, Ranica, Bergamo and will be conducted with the cooperation of:

- Hospital '*Ospedale San Giovanni di Dio*', Agrigento, Italy;
- Clinical Research Center for Rare Diseases '*Aldo e Cele Daccò*', Ranica (Bergamo), Italy
- Hospital '*Ospedale Vito Fazzi*', Lecce, Italy
- Hospital '*Ospedale Maggiore Policlinico, Mangiagalli e Regina Elena*', Milan, Italy
- University '*Università Federico II*', Naples, Italy
- Hospital '*Ospedale Ca' Foncello*', Treviso, Italy

Eligible patients will be stratified for the presence (YES or NO) of concomitant clinical conditions that could appreciably affect the rate of renal function loss over time including diabetes mellitus, 24 hour urinary protein excretion >1g, or any other evidence of concomitant renal disease without indication for specific therapy. Within each stratum patients will be randomized on a 1:1 basis to Long-acting Somatostatin (Octreotide LAR) 40 mg (treatment group) or saline solution (placebo group). Data will be collected by means of an *ad-hoc* study Case Report Form (see Appendix 1).

The general aim of the trial is to assess the efficacy of one year treatment with long-acting somatostatin analogue (Octreotide LAR) compared with placebo in slowing kidney and liver growth rate in patients with ADPKD and moderate/severe renal insufficiency (estimated GFR by MDRD 4 variables: 15-40 ml/min/1.73m^2) and to assess whether and to which extent this translates into slower renal function decline over 3-year follow-up.

Primary objectives are the followings: to compare the effect of long acting somatostatin analogue (Octreotide LAR) versus placebo on total kidney volume (TKV) change (delta TKV) as assessed by spiral computed tomography (spiral CT)

scan (short-term, one year) and to compare the effect of long-acting somatostatin analogue (Octreotide LAR) vs. placebo on the rate of GFR decline as assessed by serial measurements of the iohexol plasma clearance (long-term, three years).

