### **3.3.1.2 Three Years Primary Efficacy Parameter**

The long-term primary efficacy variable - i.e. measured GFR total slope – will be assessed with a linear regression analysis and compared with the Wilcoxon rank-sum test. Exploratory linear mixed-models using SAS PROC MIXED will be also used measured GFR repeated measures, with age, gender and baseline measured GFR as covariates. Between-groups differences in median GFR slopes and their 95% CI were determined by means of Hodges-Lehmann Estimation using the SAS PROC NPAR1WAY. Summary statistics, namely mean (sd), median, q1, q3, minimum, and maximum for measured GFR will be tabulated by nominal visit and treatment group. Moreover, relevant summary statistics will be presented for measured GFR total slope (overall and according to stratum CCC absent or stratum CCC present).

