### **3.3.3 Other Efficacy Parameters**

#### **3.3.3.1 Time to ESRD and time to doubling of Serum Creatinine or ESRD (Tables 3.53.1-3.53.2, 3.54.1-3.54.2, Figures 1 and 2)**

The time to the ESRD and the time to the composite endpoint 'doubling of serum creatinine or ESRD' will give rise to right censored data. Kaplan-Meier curves will be plotted in Figures 1 and 2 and summary statistics, including the Kaplan-Meier estimates of the proportions of patients event-free at monthly intervals, median event times and proportions of patients providing censored values, will be given in Table 3.53.1 and 3.54.1 respectively. Confidence intervals from these proportions and for the median event time calculated using Greenwood's formula will also be provided in Table 3.53.1 and 3.54.1. Cumulative event curves will be constructed using the Kaplan-Meier procedure and the Cox regression model will be used to estimate the hazard ratio for the ESRD endpoint and 'doubling of serum creatinine or ESRD' composite endpoint with the corresponding 95% CI. The model will be adjusted for age, gender and baseline serum creatinine. Participants who didn't reach the outcome of interest will be considered as right censored. Proportionality assumptions were assessed using Schoenfeld residuals. Individual patient data for the time to ESRD and time to doubling of serum creatinine or ESRD will be listed in Appendix 12 and 13

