#### **3.3.3.2 Overall, Cardiovascular and Non-cardiovascular Mortality (Tables 3.55.1 to 3.57.2 and Figures 3,4 and 5)**

Time to total death, time to cardiovascular death and time to non-cardiovascular death will be analysed as time to ESRD, outlined in Section 3.3.3.1. Kaplan-Meier curves will be plotted in Figures 3,4 and 5 while Tables 3.55.1 to 3.57.2 will contain, respectively, summary statistics associated with the

Kaplan-Meier curves, and Proportional Hazards regression model fitting details. Individual patient data for the time to death, time to cardiovascular mortality and time to non-cardiovascular mortality will be listed in Appendices 14-16.

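### Randomisation is stratified by concomitant clinical condition, but no overall treatment comparison uses the stratum; the mGFR slope test is then conservative if the stratum is prognostic

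*Supplement*

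**What the plan says.** The SAP Introduction stratifies patients by presence or absence of "concomitant clinical conditions that could appreciably affect the rate of renal function loss over time": diabetes, proteinuria above 1 g per day, or another renal disease not needing specific treatment. It adds: "Within each stratum patients will be randomized on a 1:1 basis". Later sections label the strata CCC absent and CCC present.

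The planned treatment comparisons are:

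- **TKV at one year (3.3.1.1):** ANCOVA of log TKV, "including baseline TKV, age and gender as covariates".
- **mGFR slope at three years (3.3.1.2):** the slope "will be assessed with a linear regression analysis and compared with the Wilcoxon rank-sum test", with a Hodges-Lehmann estimate and interval. The exploratory mixed model is fitted "with age, gender and baseline measured GFR as covariates".
- **ESRD, and doubling of creatinine or ESRD (3.3.3.1):** Cox regression. "The model will be adjusted for age, gender and baseline serum creatinine".
- **Mortality (3.3.3.2):** these times "will be analysed as time to ESRD, outlined in Section 3.3.3.1". First major cardiovascular event (3.3.3.3) is handled the same way.

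The Cox templates (Tables 3.53.2 to 3.57.2) list age, sex and baseline serum creatinine and no stratum term. CCC serves only to split output: baseline tables, slope summaries, Kaplan-Meier figures, and separate Section 3 tables for each stratum, including p-value rows in Tables 3.1.2 and 3.1.3.

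**The concern.** The design balances the arms on a factor that the plan expects may matter for GFR decline, and the rate of GFR decline is the three-year primary endpoint. Balance within strata removes between-stratum variation from the treatment difference. An analysis that ignores the strata still counts that variation as noise, so the reported uncertainty is larger than the design warrants. The test then rejects too rarely under the null and gives up some power. The plan adjusts for age and gender, which were not stratified on, and leaves out the one factor that was.

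**Working it through.** **Inputs.** Two-sided testing is set in 3.2. The 0.05 level appears in the footnotes to the Cox tables and is assumed here for the primary tests. The documents shown give no ALADIN 2 sample size, power, SD, CCC share or CCC effect, so there is no plan figure to reproduce. The 80 patients in the appended quality-of-life protocol belong to that sub-study. Everything below rests on assumed ranges.

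**mGFR slope, analytic.** Let p be the share with CCC and d the difference in slope between strata, in within-stratum SDs. With arms balanced within strata:

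- True variance of the treatment difference: the within-stratum value V.
- Variance used by the unstratified test: V × VI, where VI = 1 + p(1−p)d².
- Rejection therefore requires |difference|/√V > 1.960√VI.
- True type I error = 2[1 − Φ(1.960√VI)].
- Power, when the stratified test has 80% = Φ(1.960 + 0.842 − 1.960√VI).

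Lower case, p = 0.2 and d = 0.5: VI = 1 + 0.16 × 0.25 = 1.04 and 1.960√VI = 1.999. Type I error is 0.046; power is Φ(2.802 − 1.999) = 0.789.

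Upper case, p = 0.3 and d = 1: VI = 1 + 0.21 × 1 = 1.21 and 1.960√VI = 2.156. Type I error is 0.031; power is Φ(2.802 − 2.156) = 0.741.

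| p | d | VI | SE overstated by | Type I error | Power |
|---|---|---|---|---|---|
| any | 0 | 1.000 | 0% | 5.0% | 80.0% |
| 0.1 | 0.25 | 1.006 | 0.3% | 4.9% | 79.8% |
| 0.2 | 0.5 | 1.040 | 2.0% | 4.6% | 78.9% |
| 0.3 | 0.5 | 1.052 | 2.6% | 4.4% | 78.5% |
| 0.2 | 1.0 | 1.160 | 7.7% | 3.5% | 75.5% |
| 0.3 | 1.0 | 1.210 | 10.0% | 3.1% | 74.1% |

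**mGFR slope, simulated.** These formulas are normal-theory, so the rank tests were simulated directly: assumed N = 100, effect 0.58 SD, normal errors, 4000 runs.

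| p | d | Null rejection, Wilcoxon / van Elteren | Power, Wilcoxon / van Elteren |
|---|---|---|---|
| 0.2 | 0.5 | 0.047 / 0.049 | 0.777 / 0.789 |
| 0.3 | 1.0 | 0.030 / 0.050 | 0.734 / 0.797 |
| 0.5 | 1.0 | 0.024 / 0.046 | 0.714 / 0.786 |

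The rank tests behave as the formulas predict.

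**Cox models, simulated.** Assumed N = 100, treatment HR 0.5, three years of follow-up, 1500 runs, and none of the planned covariates.

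| p | Stratum HR | Mean log HR, unstratified / stratified | Mean SE | Power |
|---|---|---|---|---|
| 0.2 | 1.5 | −0.697 / −0.703 | 0.314 / 0.315 | 0.603 / 0.602 |
| 0.3 | 2.0 | −0.679 / −0.703 | 0.298 / 0.299 | 0.636 / 0.660 |
| 0.5 | 3.0 | −0.637 / −0.720 | 0.265 / 0.268 | 0.698 / 0.783 |

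The standard error hardly moves; the estimate shrinks toward no effect. In the last row the null rejection rates were 0.035 unstratified and 0.061 stratified, with a Monte Carlo error of about √(0.05 × 0.95/1500) = 0.006. Part of that power gap may therefore be simulation noise.

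**The case against.** The strongest reply is that nothing here threatens validity. The error is conservative, false positives are not inflated, and stratum results are pre-planned throughout Section 3. The first two parts stand. The third does not answer the point: per-stratum tables are subgroup displays that split the sample, and none gives a stratified overall test or estimate.

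The size is also open to challenge, and fairly. A difference of 1 SD between strata is large, and nothing in the documents supports it. The eligibility form excludes proteinuria above 3 g and HbA1c above 8%, which limits how severe these conditions can be. With few CCC patients or a weak effect, almost nothing is lost.

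Three stronger readings are tempting and not supported:

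- **That power is lost on both primary endpoints.** The Introduction ties CCC to loss of renal function and says nothing about kidney growth. The TKV model also already adjusts for baseline TKV, age and gender, so only an effect of CCC beyond those would matter.
- **That power falls to 78-72%.** Φ(2.80/√VI − 1.96) gives those values, but it treats the estimate's true variance as inflated. That contradicts balance within strata, and it cannot be combined with a type I error below 5%.
- **That the Cox standard errors are too large.** They barely change. Age, gender and creatinine adjustment may also absorb part of the stratum effect.

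**Conclusion.** The omission is certain: CCC defines the randomisation and enters no overall comparison. Its cost is not known. Under the assumed 20-30% share and 0.5-1.0 SD difference, with arms balanced within strata, the mGFR slope test runs at about 4.6% to 3.1% in place of 5%. It loses about 1 to 6 points from 80% power, and its interval is too wide for the design. The case is best supported for mGFR slope. For ESRD and the composite it holds as attenuation of the hazard ratio, negligible when the stratum effect is modest. For TKV it is conditional on CCC affecting kidney growth. This is a recoverable loss of precision that should be mended; it does not bias the trial toward a positive result.

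**What to change.** Amend the SAP at the blind review that its Introduction already schedules, before unblinding:

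- **mGFR slope:** replace the plain Wilcoxon test by the van Elteren test stratified by CCC, with a stratified (aligned) Hodges-Lehmann estimate and interval.
- **Mixed model:** add CCC and CCC-by-time.
- **TKV ANCOVA:** add CCC as a factor, for consistency with the design.
- **ESRD and composite Cox models:** stratify by CCC or adjust for it, and show this in Tables 3.53.2 and 3.54.2.

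The stratum is known for every randomised patient, so no data collection is needed. The cost is modest but not nil. The primary slope test and estimator change and need new programming, and there is little to gain if one stratum is very small or events are few. For that reason the sparser mortality and cardiovascular models need not be stratified by default.
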